### Recruitment

Completion eFTR after incomplete excised T1 CRC is currently offered to patients as an alternative to surgery in clinical practice. After case discussion in a colorectal MDT, recruitment for the study will be performed by gastroenterologists, gastroenterology fellows or research nurses in the participating centers. Eligible patients will be informed about the study aims, the prospective data collection, the eFTR procedure and follow-up procedures and will receive an informed consent form. Patients will hand in the signed informed consent forms to a member of the study team in the participating centers. Patients will be given as much time as needed to make an informed decision regarding participation.

### Plans for assessment and collection of outcomes

Patient data will be collected from the electronic patient databases and recorded in an online secured database (Castor, CIWIT BV, Amsterdam). The PhD student with help of a research nurse will coordinate and regularly visit all participating centers to collect all accomplished data in the database. During surveillance the PhD student will collect all data regarding the surveillance visits in the eCRFs and will monitor study adherence in the participating centers.

### Plans to promote participant retention and complete follow-up

The PhD student and research nurse will monitor study adherence in the participating centers. The PhD student will inform the participating hospitals in case follow-up is not performed on time. Additionally, four patients will be asked to join our study patient advisory board and evaluate yearly patient participation by hearing the report of the research team. The patients’ input helps ensuring optimal patient participation, patient adherence to the five years surveillance and communicate the outcomes to the patient organisation.

### Data management and confidentiality

Patients will be coded by a numeric code (pseudonymised) and only the local investigators and project leader will be the ones to have access to this code. The code lists will be stored digitally on the protected hard disc at the local center that included and treated the subject. The patient data will be recorded in an online secured database (Castor, CIWIT BV, Amsterdam). All study investigators at each study site will have access to the online database of their own site and will be able to insert data.

### Statistical methods for primary and secondary outcomes

For our primary analysis all performed eFTR procedures in patients in whom the primary outcome (luminal local tumor recurrence rate after scar resection) can be assessed will be included. Thus patients in whom the procedure could not be performed for technical reasons or needing additional surgery due to the presence of high-risk features following completion eFTR will not be included for primary analysis.

For secondary analysis regarding feasibility of completion eFTR all included eligible patients will be analysed irrespective of the received completion eFTR or performed additional surgery.

Descriptive statistics will be used to describe patient, colonoscopy and eFTR characteristics for primary and secondary outcomes. Variables will be reported as mean with standard deviation in case of continuous and normally distributed variables, as median with an interquartile range (IQR) in case of non-normally distributed continuous variables, and as percentages in case of count or categorical variables. will use logistic regression with baseline variables to identify predictors for a successful completion eFTR.

The confidence interval of the 5 year disease-specific survival rate and overall survival rate will be calculated. Kaplan–Meier analysis will be used to estimate survival over time.

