### Trial design

This nationwide prospective observational multicenter study aims to investigate the feasibility and oncological safety of eFTR as completion treatment after previous potential incomplete resection of low-risk T1 CRC. Patients referred for completion eFTR for low-risk T1 CRC with positive resection margins < 0.1 mm (R1) or indeterminate margins (Rx) are eligible for participation in this prospective cohort study. Patients will be followed by protocolized surveillance during 5 years.

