#### Endoscopic follow-up

Endoscopic surveillance for lesions located in the colon will be performed by yearly eFTR scar checks at 12, 24, 36, 48 and 60 months. In patients with T1 rectal cancer endoscopic surveillance of the eFTR scar will be performed every 6 months during the first two years followed by yearly scar checks at 36, 48 and 60 months. According to the Dutch guideline, scar checks will be combined with a full colonoscopy at 12 months and 48 months for CRC surveillance [27]. The eFTR scar will be thoroughly inspected with HD WLE and (digital) chromoendoscopy. Endoscopists preferably take a minimum of three photos of the scar. Scar biopsies (3 biopsies) will be taken at every surveillance, even from scars without signs of macroscopic recurrence. Endoscopic and histological findings compatible with granulation tissue or reactive changes can be left untreated. Recurrent/residual low-grade dysplastic adenoma or a sessile serrated lesion can be treated endoscopically with conventional treatment strategies. When high-grade dysplasia or submucosal invasive cancer is found, a tattoo (SPOT) should be placed followed by case discussion in a colorectal MDT.

Local luminal tumor recurrence is defined as the presence of any adenocarcinoma at the site of the eFTR scar at follow-up colonoscopy. Further treatment and follow-up will be planned individually depending on histology and further staging procedures in the participating centers.

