### Sample size

Up-to-date, literature is scarce with regard to local luminal recurrence rates after endoscopic incomplete resection of T1 CRC (R1/Rx resections) for low-risk T1 CRC. A recent study showed local recurrence rates of 4.5% (4/89) after full-thickness resections of incomplete resected presumed low-risk T1 CRC. However, in this study histologic reassessment was not performed before resection and retrospective histologic revision showed high-risk factors for LNM in 3 out of 4 local recurrences [41].

Another study observed a local recurrence rate of 1% (1/102) during almost four years of follow-up after minimally invasive transanal surgery [42]. Considering that literature is limited, the upper limit of its 95% one-sided confidence limit may extend to 4.6%. With already being frequently used in daily practice and considering that the follow-up duration in the current study will by five years (instead of four), we opt to qualify eFTR as unsafe if the upper 95% one-sided confidence limit of its related local recurrence rate after five years extends beyond 6.6%.

A single sample size of 137 patients will have at least 86% power to detect this non-inferiority limit of 6.6% using a one-sided exact test with a significance level of 0.05 for maximum actually observed local recurrence rates of 2% over five years (twice the possibly underestimated local recurrence rate over four years of 1% for minimally invasive surgical treatment). To correct for potential drop-out patients in whom the primary outcome cannot be assessed the sample size will be adjusted to 153 (potential drop-out rate of 10%). These drop-out cases are patients with indication for additional surgery when histopathology review reveals high-risk features (i.e. poor differentiation grade, lymphovascular invasion and/or high-grade tumor budding) for LNM or eFTR is technically impossible. If during 5 years of follow up, more than 5 local luminal recurrences are observed -which implies that the upper limit of the confidence interval will exceed the non-inferiority limit- our study fails to establish oncological safety for completion endoscopic full-thickness resection after previous incomplete resection of low-risk T1 CRC.

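### The 5-year safety rule assumes every analysed patient is observed to 60 months, and the article does not say how patients lost earlier enter the rate

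*Protocol article*

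**What the plan says.** The Sample size section calls eFTR unsafe if the "upper 95% one-sided confidence limit of its related local recurrence rate after five years extends beyond 6.6" per cent. The size of 137 is derived "using a one-sided exact test with a significance level of 0.05", and the criterion is then turned into a count: "If during 5 years of follow up, more than 5 local luminal recurrences are observed", safety is not established. The number is raised to 153 for 10% drop-out. That drop-out is described as patients with high-risk histology who need surgery and patients in whom eFTR is technically impossible.

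The section Statistical methods for primary and secondary outcomes takes performed procedures in "patients in whom the primary outcome (luminal local tumor recurrence rate after scar resection) can be assessed will be included". It then names two exclusions: technical failure, and patients "needing additional surgery due to the presence of high-risk features following completion eFTR will not be included for primary analysis". No minimum follow-up is given. Directly after the disease-specific and overall survival rates it says that Kaplan-Meier "analysis will be used to estimate survival over time". No time-to-event method is named for recurrence.

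Under Endoscopic follow-up, "Local luminal tumor recurrence is defined as the presence of any adenocarcinoma at the site of the eFTR scar at follow-up colonoscopy". Under Trial design, "Patients will be followed by protocolized surveillance during 5 years".

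**The concern.** The endpoint can be seen only at a scar inspection. A patient who stops attending at month 18 has an unknown status at month 60, and a binomial proportion has no place for such a patient. Either the patient stays in the denominator as non-recurrent, or the patient is dropped as not assessable. Recurrences found before other patients left would naturally stay in the count under both choices. The two choices err in opposite directions, and the article's wording permits both.

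At stake are the primary estimate, its upper limit and the real error rate of the comparison with 6.6%. In a single-arm study, an assessable set that is settled only once the data are known also leaves the safety verdict open to that choice.

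**Working it through.** **Inputs from the article.** N = 137; margin 6.6%; assumed true rate 2%; one-sided exact test at 0.05; stated power at least 86%; 10% drop-out giving 153.

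**Inputs assumed, because the article gives none.** A share q of the 137 is lost before 60 months, with q = 5%, 10% or 15%. Recurrence has a constant hazard, approximated as linear over 5 years. Exits are uniform over 5 years and unrelated to recurrence.

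**Step 1: reproduce the plan's figures.** The largest c with P(X ≤ c | 137, 0.066) ≤ 0.05 is c = 4:
- P(X ≤ 4 | 137, 0.066) = 0.0481
- P(X ≤ 4 | 137, 0.02) = 0.859, the stated 86%
- 137 / 0.9 = 152.2, rounded up to 153

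The design therefore reproduces with a cut-off of 4 and all 137 fully observed.

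**Step 2: what the drop-out allowance covers.** 153 × 0.9 = 137.7. If the two named early exclusions take the whole 10%, nothing is left for loss during the five years.

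**Step 3: lost patients kept as non-recurrent.** On average a lost patient is observed for half of the period, so the expected crude rate is 0.066 × (1 − q/2). The false-safe probability is P(X ≤ 4 | 137, crude rate).

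| q | Crude rate | False-safe probability |
|---|---|---|
| 0 | 6.60% | 4.8% |
| 5% | 0.066 × 0.975 = 6.44% | 5.6% |
| 10% | 0.066 × 0.95 = 6.27% | 6.4% |
| 15% | 0.066 × 0.925 = 6.11% | 7.4% |

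**Step 4: lost patients dropped, their earlier recurrences kept.** The denominator is the completers plus the lost patients who had already recurred: (1 − q) + q × 0.033.
- q = 10%: 0.0627 / (0.90 + 0.0033) = 6.9%
- q = 15%: 0.06105 / (0.85 + 0.00495) = 7.1%

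The bias is now upward, against eFTR.

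**Step 5: a fixed count does not follow the number observed.** One-sided 95% Clopper-Pearson upper limits:
- 4/137: 6.56%, below 6.6%
- 4/136: 6.60% (6.604%), above 6.6%
- 4/123: 7.29%, above; 3/123: 6.18%, below

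One patient fewer in the denominator already reduces the permitted count from 4 to 3.

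**The case against.** The strongest reply has four parts.

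**The formal criterion is a confidence limit, and censoring rules belong elsewhere.** The first half is right: the count is presented as what the limit implies. But the article does not merely omit detail. It fixes an exact binomial test, a count, an assessability condition and a drop-out definition that together presuppose complete follow-up.

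**Death and removal of the scar site do not bias the count.** This stands. A reader might infer that counting patients who die, or whose bowel segment is resected, as non-recurrent pulls the rate down. A cumulative incidence with death and removal as competing events also leaves those patients without a recurrence, and without censoring it equals the raw proportion. For them the question is which estimand is wanted. Only loss to follow-up or missed inspection produces the bias in Step 3. Nor is site removal wholly unaddressed: surgery for high-risk features after eFTR is excluded from the primary analysis. The text is silent on surgery after an R1/Rx eFTR without such features, which the Follow-up section refers to multidisciplinary discussion, and on later resections.

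**The size is unknown.** This also stands. The article gives no loss rate and describes active retention: adherence monitoring, alerts to hospitals when follow-up is late, and a patient advisory board. At 5% loss the effect is small (4.8% to 5.6%).

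**No direction is established.** Correct. The text says neither that lost patients are kept nor that they are dropped. That ambiguity is part of the defect.

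A reader might also combine this point with the written limit of more than 5 recurrences and arrive at larger error rates. At 137 patients, 5 events already give an upper limit of 7.52% with complete follow-up. That is a separate error and is not counted here.

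**Conclusion.** The point holds for patients lost to follow-up, or not inspected, before 60 months. The stated error rate and power apply only if all 137 analysed patients are observed for five years. The sample size leaves no allowance for later loss, and the analysis set does not say what happens to these patients.

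Under the assumptions shown, 5% to 15% loss raises the false-safe risk from 4.8% to between 5.6% and 7.4% if they are kept as non-recurrent. Alternatively it inflates a true 6.6% to about 6.9% (10% loss) or 7.1% (15%) if they are dropped and their recurrences kept. These are moderate shifts. The documents do not support a claim that the study is biased towards safety in particular, or that attrition will be high. The analysis should nevertheless be changed, because the remedy is cheap and removes the dependence on an undefined denominator.

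**What to change.** Make the primary estimate the cumulative incidence of luminal recurrence at 24 and 60 months after eFTR. Censor at the last scar inspection, and treat death and later removal of the eFTR site as competing events. State this as the estimand. Compare the one-sided 95% upper limit at 60 months with 6.6% in place of a fixed count, and name in advance an interval method suited to few events under competing risks. Keep the exact binomial as a sensitivity analysis, with its denominator defined. State that the drop-out allowance does not cover loss during follow-up, or extend it.

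**Cost.** Wording and some programming; no new data and no change to patient care. The limit will be wider and power somewhat below the stated 86% if follow-up is incomplete. To retain 137 fully followed patients after the 10% already allowed, recruitment would have to rise from 153 to 137 / (0.9 × 0.95), that is 161, at 5% further loss, or to 137 / (0.9 × 0.9), that is 170, at 10%. If recruitment stays at 153, the loss of power should be acknowledged.

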#### Histopathology handling

The resection specimen is stretched and pinned down on paraffin or cork before immersed into formalin. Histopathological analysis is performed by a gastrointestinal pathologist according to daily clinical practice. In case of presence of residual adenocarcinoma, deep and lateral resection margins will be assessed as well as all histological risk features (differentiation grade, depth of invasion, lymphovascular invasion and tumor budding (grade 2 or 3)).

In the eFTR specimen, the pathologist will assess the presence of reactive changes compatible with scar tissue in the specimen. Definite histopathological confirmation of complete scar resection is known to be difficult and might not always be possible. In case the pathologist is not able to histologically confirm complete scar resection, further treatment will be based on the macroscopic completeness of scar excision and patients will be followed according to protocol.

In addition, central review of all resected eFTR specimens will be performed after all patients are included in the study. The central review will be performed by two independent expert gastrointestinal pathologists. In this review, the presence of neoplasia, scar tissue and evaluation of completeness of excision regarding both neoplasia and scar will be evaluated by both expert pathologists. In cases without consensus, meetings will be organized to discuss discrepancies to reach consensus. In case no consensus can be reached, a third expert pathologist will be consulted.

H&E slides of all resected eFTR specimens will be collected from the different laboratories and digitalized at the Amsterdam UMC for review. After digitalizing the slides will return to the laboratories to ensure the completeness of pathology archives and optimal patient care.

In case of unexpected findings, the treating physician will be informed to discuss further treatment options with the patients after colorectal MDT discussion. Outcomes of these cases will be recorded in the study database.

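### The primary analysis set excludes patients by an indication for surgery found after eFTR, with no time limit, so patients with an assessable scar, and even known recurrences, can be left out

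*Protocol article*

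**What the plan says.** The protocol article's section on statistical methods for primary and secondary outcomes defines the primary set in two sentences. The first includes all performed eFTR procedures in patients whose local luminal recurrence can be assessed. The second, offered as its consequence, leaves out "patients in whom the procedure could not be performed for technical reasons or needing additional surgery due to the presence of high-risk features" after completion eFTR.

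The Sample size section describes the same group as drop-outs whose primary outcome cannot be assessed: "patients with indication for additional surgery when histopathology review reveals high-risk features", or those in whom eFTR is technically impossible. It does not say which review is meant. Neither section gives a date after which a patient can no longer be excluded.

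Three other sections bear on this:

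- **Follow-up:** residual cancer with high-risk features, or an R1/Rx eFTR, is discussed in a multidisciplinary team for further treatment options. Surgery is not automatic.
- **Histopathology handling:** the local pathologist assesses high-risk features when residual cancer is present. In addition, "central review of all resected eFTR specimens will be performed after all patients are included in the study". The items listed for that later review are neoplasia, scar tissue and completeness of excision.
- **Endoscopic follow-up:** scar checks start at 6 months (rectum) or 12 months (colon) and run to 60 months.

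**The concern.** The two sentences of the definition do not select the same patients. A patient with high-risk features in the eFTR specimen who is advised to have surgery, but stays on surveillance, has a scar that can be inspected and biopsied. The first sentence keeps that patient and the second removes the patient. The analyst has to choose, and the choice affects patients at higher risk of recurrence.

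The missing time limit adds a second problem. An exclusion decided after a positive scar check is as permissible under the text as one decided from the first pathology report. If a recurrence prompts another look at the specimen and high-risk features are then recognised, the patient meets the exclusion and leaves both numerator and denominator.

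Both routes lower the estimated recurrence rate. With about 137 patients and an acceptance limit near four events, the conclusion on oncological safety is sensitive to a single patient.

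**Working it through.** **Inputs, all from the Sample size section.** The test is specified "using a one-sided exact test with a significance level of 0.05". eFTR is called unsafe "if the upper 95% one-sided confidence limit of its related local recurrence rate after five years extends beyond 6.6" per cent. The section states "A single sample size of 137 patients will have at least 86% power", for "maximum actually observed local recurrence rates of 2% over five years". Allowing 10% drop-out gives 153.

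**Step 1: reproduce the plan.** The one-sided 95% Clopper-Pearson upper limit is U(x, n) = 0.95 quantile of Beta(x + 1, n − x).

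- U(4, 137) = 6.56%, which passes. U(5, 137) = 7.52%, which fails. So at most 4 recurrences are allowed among 137.
- Type I error: P(X ≤ 4 | 137, 0.066) = 0.0481.
- Power: P(X ≤ 4 | 137, 0.02) = 0.8588, the stated 86% after rounding.
- Drop-out: 137 / 0.90 = 152.2, rounded up to 153.

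The section also words failure as more than 5 recurrences. That does not match the 6.6% limit at 137: allowing 5 gives a type I error of 0.1051. I use the 6.6% limit below because it reproduces the stated alpha and power.

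**Step 2: effect of removing one recurrence.**

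| Before | Upper limit | After | Upper limit |
|---|---|---|---|
| 5/138 | 7.47%, fails | 4/137 | 6.56%, passes |
| 5/137 | 7.52%, fails | 4/136 | 6.604%, just fails |

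One removal reverses the result from 138 patients. From exactly 137 it narrowly does not, because the allowance falls to 3 below 137. Under the more-than-5 wording, 6/138 fails and 5/137 passes, so one removal reverses that rule as well.

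**Step 3: effect on the false-pass rate, under assumptions.** Let E ~ Bin(137, 0.066) be the recurrences at the limit itself. Let each be removed from numerator and denominator with probability r, and let K be the number removed. The result passes if U(E − K, 137 − K) ≤ 6.6%. The allowance is 4 at n = 137 and 3 for n from 116 to 136, so the pass probability is

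P(Bin(137, 0.066(1 − r)) ≤ 3) + P(E = 4) × (1 − r)^4, with P(E = 4) = 0.0303.

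| r (assumed) | First term | Second term | Chance of passing |
|---|---|---|---|
| 0 | 0.0178 | 0.0303 | 4.8% |
| 10% | 0.0346 | 0.0199 | 5.5% |
| 20% | 0.0653 | 0.0124 | 7.8% |
| 25% | 0.0883 | 0.0096 | 9.8% |
| 50% | 0.3345 | 0.0019 | 34% |

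The document gives no value for r. The table shows sensitivity and does not forecast.

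**The case against.** The strongest reply is that the assessability sentence governs. The exclusion follows from it and merely illustrates who cannot be assessed, and the Sample size section also speaks of patients whose outcome cannot be assessed. On that reading, a high-risk patient under surveillance, or one with an observed recurrence, stays in. This is a fair reading, but not the only one: both sections word the exclusion by need or indication, and the literal wording removes such patients.

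A reader might go further and infer that the late central review of eFTR specimens is the planned route by which recurrences are relabelled and dropped. The document does not say so. The items listed for that review do not include high-risk features. Those features are read locally in routine practice, and exclusions made then would normally precede the first scar check. The drop-out definition does cite a histopathology review, and the central review is the only one named after inclusion, so the route is possible but not stated.

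A reader might also carry over the cited cohort, in which "retrospective histologic revision showed high-risk factors for LNM in 3 out of 4 local recurrences". That proportion should not be transferred. The cohort had no histological reassessment before resection, whereas here every index specimen is centrally reviewed before inclusion. Relabelling here would also need residual cancer in the eFTR specimen. Small values of r are therefore easier to defend than large ones, and at 10% to 20% the inflation is modest.

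Leaving out technical failures is not a defect of this endpoint. Recurrence is defined at the eFTR scar and cannot arise where no eFTR was done. Nor does the feasibility rate give the number of such exclusions, because a performed but incomplete excision fails feasibility and is still a performed eFTR.

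Finally, masking and sensitivity sets are often left to an analysis plan. That is true, but this article itself states the primary set, in terms that conflict.

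**Conclusion.** The point holds as a defect in how the primary set is defined. The exclusion is tied to an indication for surgery, has no time limit, and conflicts with the assessability rule before it. It can remove higher-risk patients with an assessable scar, and it does not rule out removal after a recurrence is known. The direction is towards a lower recurrence rate.

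The size is unknown. At a true rate of 6.6%, the chance of passing rises from 4.8% to 5.5% or 7.8% if 10% or 20% of recurrences are removed, and to 9.8% or 34% at 25% or 50%. These figures rest on an assumed removal probability, independent removals, 137 patients before removal, and the exact 6.6% limit. The document does not show that anyone intends to remove recurrences. It shows only that the text allows it, in a design where one event can decide the result. The change is cheap and worth making.

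**What to change.** Rewrite the definition of the primary set along these lines:

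- Every patient in whom eFTR was performed belongs to the primary set.
- A patient is censored at the date on which the eFTR site is actually removed surgically, not when surgery is indicated or advised. A recurrence found before that date counts.
- Pathology review after eFTR, including the central review, cannot change membership. Its findings feed a sensitivity analysis only.

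Use the same wording for drop-out in the Sample size section, and say how patients censored before five years enter the exact test, which takes a simple proportion.

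The cost is wording plus one sensitivity analysis. The protocol already records subsequent treatment and follow-up for these cases, so no new data item is evident. The estimate may become slightly less favourable. A larger analysed set does not relax the rule: even if all 153 had a performed eFTR and counted in full, at most 4 recurrences would be allowed (4/153: 5.88%; 5/153: 6.75%), with power at 2% of 80.7% instead of 85.9%.
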